### HIIT Group

The HIIT protocol has been adopted from the studies by Giannaki et al [52] and Wu et al [43] and has been slightly modified. The intervention will be conducted over a period of 10 weeks, and the participants will complete 3 training sessions per week. Each HIIT training program will last for 30 minutes. The session will include a 10-minute warm-up period, followed by a 15-minute HIIT workout, and a 5-minute period of stretching to cool down. The exercise will include repeated, high-intensity intermittent bursts of vigorous activity at maximal effort. The HIIT will mainly include bodyweight exercises (eg, push-ups, squats, and lunges) that disregard equipment use. The intensity during the workout will be set to 85%-95% of the individual’s maximum HR (Textbox 1). The exercise was designed by a registered physiotherapist with more than 10 years of clinical experience. A half-day training workshop will be provided to the personal trainer to ensure that they know the exercise and can demonstrate them to the participants.

Design of the high-intensity interval training (HIIT) program.
**Study design for HIIT**
Start: 10-minute warm-up.HIIT program: Every circuit takes 3 minutes 45 seconds.Work: 15 seconds.Rest: 10 seconds.Work: 15 seconds.Rest: 20 seconds.Work: 15 seconds.Rest: 30 seconds.Work: 15 seconds.Rest: 40 seconds.Work: 15 seconds.Rest: 50 seconds.Repeat 4 circuits.End: 5 minutes of stretching.The *work* period indicates the short-duration, full-effort exercise to boost the heart rate (HR) to 58%-95% or to the maximum HR.The *rest* period indicates the active recovery with light stepping or *jumping jack* exercise at the effort to achieve 40%-50% of the maximum HR [53].

The HIIT and aerobic exercise groups will be led by a certified personal trainer with at least three years of experience in guiding adolescents in group exercise. In terms of the duration of intervention for the HIIT and aerobic exercise groups, research has shown that approximately 30 minutes is the ideal session length for an HIIT work out with an HR >90% for 3 days per week over a period of 10 weeks. For aerobic exercise, research has revealed that participants who exercise 3 times per week for 45-minute sessions over 10 weeks exhibited improved mental health. By contrast, exercising for >90 minutes per session could lead to poor mental health, which includes physical and mental exhaustion [54]. To prevent symptoms of overreaching (eg, fatigue, mood disturbance, and disrupted sleep), the aforementioned intensity and duration of the exercise will be applied in this study. Aerobic exercise and HIIT training will be conducted in the fitness room of a local sports center hosted by the Leisure and Cultural Services Department in Hong Kong [55].

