### Aerobic Exercise Group

Following the exercise recommendation in the literature review and the study by Ranjbar et al [37], this study will conduct the aerobic exercise classes over a period of 10 weeks. The participants will complete 3 training sessions per week. In addition, each aerobic training program will last for 1 hour. The session will include a 10-minute warm-up period, followed by a 45-minute aerobic workout, wherein the participants can choose to use either a treadmill, a cycle ergometer, or a rowing ergometer. After the workout, a 5-minute period of stretching will be provided for cooling down. The intensity during the workout will be set at 40%-55% of the individual’s maximum HR [37].

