### HR Monitoring

To monitor the intensity of the training during the program, the participants are required to wear HR monitor watches (Polar Electro Oy). The recorded HR data will be uploaded to a computer and will be checked regularly by investigators to determine whether the participants could reach the target HR during the exercise. Furthermore, the length of time (number of minutes and average session duration) when the participant reaches the HR targets will be recorded. The participants will also be encouraged to achieve the target HR during the session. The maximum HR will be calculated according to the age-based formula (220-age). To ensure their safety and manage unexpected situations, a subjective measurement of physical exertion (using Borg scale 6-20) will also be monitored during every training session by an assistant trainer [56].

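### Textbox 1 sets the HIIT work-bout heart-rate floor at 58%, against 85% of maximum HR in the text that cites it; this is almost certainly a digit transposition, and the target-HR check could inherit it

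*Protocol article*

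**What the plan says.** All the statements are current text in the Methods of the protocol article.

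- **HIIT Group** (body text, ending in a reference to Textbox 1): "The intensity during the workout will be set to 85%-95% of the individual’s maximum HR". The same section describes the exercise as "repeated, high-intensity intermittent bursts of vigorous activity at maximal effort".
- **Textbox 1 (Study design for HIIT), work period:** "full-effort exercise to boost the heart rate (HR) to 58%-95% or to the maximum HR".
- **Textbox 1, rest period:** active recovery "at the effort to achieve 40%-50% of the maximum HR".
- **Text after Textbox 1**, giving the rationale for session length: "approximately 30 minutes is the ideal session length for an HIIT work out with an HR >90% for 3 days per week".
- **Aerobic Exercise Group:** "The intensity during the workout will be set at 40%-55% of the individual’s maximum HR".
- **HR Monitoring:** investigators review the uploaded recordings to "determine whether the participants could reach the target HR during the exercise", and the length of time "when the participant reaches the HR targets will be recorded". Participants are also coached toward the target. No percentage is given in this section.

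**The concern.** The body text cites Textbox 1 for its intensity figure, and Textbox 1 gives a different figure. The upper limits agree at 95%; the lower limits are 85% and 58%.

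This number is the intensity prescription of one of the two regimens that the second research question compares. Textbox 1 is also the only place in the article with the circuit-level design, so a trainer or a replicating group would naturally work from it. HR Monitoring relies on a target without saying what it is, so a reader must go back to two statements that disagree. If the Textbox line were applied as printed, effort barely above the aerobic arm's band would count as on-target HIIT. The fidelity record could then not show that the two arms differed in intensity as intended.

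**Working it through.** **Can both statements be true?** The body text refers to the workout and the Textbox to the work bouts only. That does not reconcile them. Recovery is set at 40%-50%, so the work bouts are the part of the workout that must reach the 85%-95% band. Their floor cannot sensibly lie below it.

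**Which figure is meant?** Four things point to 85%: the body text's own range, its description of maximal effort, the description of full effort in the Textbox sentence itself, and the rationale's reference to heart rates above 90%. The digits 5 and 8 are the same in both figures and the upper limit is the same. Transposition is an inference, but a strong one.

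**The phrase before the maximum HR.** Read literally, the Textbox also permits bouts up to the maximum. The rest-period sentence that follows expresses its range as a percentage of the maximum HR, so the phrase is probably a slip for the same construction. I do not count it as a second conflict.

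**Size in beats per minute.** Inputs: age 12 to 15 (Participants); maximum HR = 220 − age (HR Monitoring).

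Maximum HR: 220 − 12 = 208 bpm; 220 − 15 = 205 bpm.

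| Level | Age 12 | Age 15 |
|---|---|---|
| 50% (HIIT recovery ceiling) | 104.0 | 102.5 |
| 55% (aerobic ceiling) | 114.4 | 112.8 |
| 58% (floor as printed) | 120.6 | 118.9 |
| 85% (floor in body text) | 176.8 | 174.3 |
| 95% (upper limit in both) | 197.6 | 194.8 |

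Differences (percentage points × maximum HR):

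- Between the two floors: 27 points = 56.2 bpm (age 12), 55.4 bpm (age 15).
- Floor above the aerobic ceiling: as printed, 3 points = 6.2 bpm at both ages; at 85%, 30 points = 62.4 and 61.5 bpm.
- Floor above the recovery ceiling: as printed, 8 points = 16.6 and 16.4 bpm; at 85%, 35 points = 72.8 and 71.8 bpm.

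**Is the rest of Textbox 1 sound?** Work per circuit is 5 × 15 = 75 s. Rest is 10 + 20 + 30 + 40 + 50 = 150 s. The total is 225 s, which is the stated 3 min 45 s. Four circuits give 15 minutes, the stated workout length, made up of 5 minutes of work and 10 of recovery. The timing reproduces exactly, so the fault is confined to the heart-rate line.

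**Exposure.** The line governs 5 minutes of work bouts per session. Over 10 weeks × 3 = 30 sessions that is 150 minutes per participant, assuming full attendance.

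**The case against.** The strongest reply is that this is a copy-editing slip. The correct value is already in the HIIT Group section, and a careful reader would infer it. Trainers told to elicit full effort would not coach to 58%, and delivery has other supports: a physiotherapist-designed programme, a trainer workshop and exertion ratings in every session. The harm arises only if the Textbox is applied literally. No decision rule uses time at target, and the repeated-measures ANOVA does not use it either.

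Much of this stands. The effect on the HR check is possible, not certain, and I claim no effect on the outcome analysis or the sample size. What does not follow is that the error can be left. It is a wrong operating figure for a randomised arm, and it feeds a check and a record that name no figure of their own.

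Two narrower replies concern the remedy. One is that writing 95% of the maximum imposes a ceiling the Textbox may not intend. The body text already sets that upper limit, so the correction follows the protocol. The other is that the body text attaches 85%-95% to the whole workout, although 10 of its 15 minutes are recovery. Tying the band explicitly to the work bouts in the HR check deals with this without rewriting the HIIT Group section.

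**Conclusion.** The concern holds. Two current statements give contradictory floors for the HIIT work bouts, 27 percentage points or about 55-56 bpm apart at ages 12 to 15. With the printed floor, the gap to the aerobic ceiling falls from about 62 bpm to about 6 bpm.

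These figures measure the misprint; they do not estimate any change in the training delivered. They rest on the protocol's own age range and maximum-HR formula. The contradiction itself needs no assumption. That 85% is the intended value is an inference from context, held with high confidence. The consequence is limited to the intensity check, the time-at-target record, the coaching toward target, and replication from the Textbox.

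**What to change.** In Textbox 1, change the work-period range to 85%-95% of the maximum HR. In HR Monitoring, apply that band as the HIIT work-bout target when checking and recording attainment. The HIIT Group section needs no change.

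The cost is a one-line correction to the Textbox before training starts, with the same band named in the monitoring instructions. It needs no new measurements and does not alter the analysis.

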### HR Monitoring

To monitor the intensity of the training during the program, the participants are required to wear HR monitor watches (Polar Electro Oy). The recorded HR data will be uploaded to a computer and will be checked regularly by investigators to determine whether the participants could reach the target HR during the exercise. Furthermore, the length of time (number of minutes and average session duration) when the participant reaches the HR targets will be recorded. The participants will also be encouraged to achieve the target HR during the session. The maximum HR will be calculated according to the age-based formula (220-age). To ensure their safety and manage unexpected situations, a subjective measurement of physical exertion (using Borg scale 6-20) will also be monitored during every training session by an assistant trainer [56].

### Promoting Participants’ Adherence to Exercise

Given that adolescent girls and boys alike may have difficulty in starting and adhering to a regular exercise program, several approaches will be conducted to promote their adherence to such programs. First, to develop an enjoyable session, fun warm-up and cool-down activities or games will be included, and participants will work with their preferred partner. To create a supportive environment, a reward and peer support system will be incorporated (eg, for pairs who provide verbal encouragement and support their peers and for their hard work during the HIIT sessions). In addition, a certificate will be awarded to recognize the participants who exert outstanding effort and dedication during the workout. Thus, positive feedback and motivation are encouraged among the partners. To promote autonomy, participants will be allowed to choose the music, select particular exercises to be completed during the workout, and choose a workout when the exercise has been mastered [39]. Participants’ responses to the intervention and reasons for early withdrawal during the intervention will also be documented in the intervention logs and the content analyzed.

### Outcome Measures

The SES data will be obtained from 2 independent sources, namely, self-reported parent questionnaires (including parents’ income and education level) and the school-reported government subvention record. Parental education will be assessed based on a 4-point scale, ranging from 1 (*primary school*) to 4 (*master’s degree or above*). The family’s monthly income will also be measured using a 23-option item with options in Hong Kong Dollar from 1 (*none*) to 23 (HK$ 32,000-$ 33,999; US $4000-$4400).

The low-SES category will be constructed based on the calculation of the income-to-needs ratio, which will be calculated by dividing the total family income by the poverty threshold for the appropriate family size following the Hong Kong government’s calculation. Families living below the poverty line with an income-to-needs ratio between 0 and 1 [57] will be classified as having low SES. The question of whether they have received financial income from several sources, including wages, family members or friends, a CSSA, an old age allowance and other government assistance, pensions, rental income, investment income, and other income will also be asked as supplementary information.

### Measures of the 3 Indicators of Mental Health

#### Cognitive Function

A range of neuropsychological tests from the Millisecond software [58] will be administered to the participants. A computerized battery of neuropsychological tests to measure the 3 core executive functions would include the Stroop Color-Word Test (inhibition), the Digit Span Test (working memory), and the Wisconsin Card Sorting Test (cognitive flexibility). These neuropsychological tests have been proven to be valid and reliable measures of adolescents’ cognitive functions in previous research [59]. The author has been using these 3 executive functioning tests to measure adolescents’ cognitive functions [60].

#### Well-Being

##### Enjoyment

A short Chinese version of the Physical Activity Enjoyment Scale (S-PACES) [61] will be used to measure their enjoyment before and after exercise. The S-PACES includes 7 negatively worded items (eg, “It is not at all interesting”) anchored on a 5-point Likert scale that ranges from 1 (*disagree a lot*) to 5 (*agree a lot*). The internal consistency of the S-PACES is high (Cronbach α=.96) [61].

##### Self-efficacy

A Chinese adaptation of the General Self-Efficacy Scale [62] will be administered to measure the adolescents’ self-efficacy. The General Self-Efficacy Scale contains 10 items (eg, “I can constantly manage to solve difficult problems if I try hard enough”), with responses ranging from 1 (*not at all true*) to 4 (*exactly true*). The internal consistency and reliability are 0.76-0.90 and 0.80, respectively.

##### Life Satisfaction

The Chinese version of the Satisfaction with Life Scale [63] will be used to measure life satisfaction. This scale is a short 5-item (eg, “I am satisfied with my life”) scale based on a 7-point rating scale that ranges from 1 (*strongly disagree*) to 7 (*strongly agree*). The Satisfaction with Life Scale has demonstrated a good reliability coefficient of 0.82 [63] and has been used in previous research using Chinese samples (Cronbach α=.84) [64].

#### Ill-Being

##### Depression, Anxiety, and Stress

The Chinese version of the 21-item Depression Anxiety Stress Scale [65] will be used to measure depression (eg, “I felt that I lack something to look forward to”), anxiety (eg, “I felt that I was close to panic”), and stress (eg, “I found it difficult to relax”) among adolescents. The respondents will be asked to rate the items using a 4-point combined severity-frequency scale that ranges from 0 (*not applicable to me at all*) to 3 (*extremely applicable to me*) based on their experiences related to each item over the past week. The Cronbach α for the depression, anxiety, and stress subscales is .83, .80, and .82, respectively, which indicates good reliability. The 21-item Depression Anxiety Stress Scale has been used in a previous study involving a Chinese sample [66].

##### Mood

The Chinese version of the Brunel Mood Scale [67] will be created based on the study by Terry et al [68] to assess the mood among Chinese students and adults. The Chinese version of the Brunel Mood Scale is a 23-item inventory with the following 5 negative mood dimensions: anger, confusion, depression, fatigue, and tension. Respondents will be asked to indicate their feelings (eg, angry, unhappy, or nervous) using a 5-point Likert scale that ranges from 0 (*not at all*) to 4 (*extremely*). All subscales have achieved good internal consistency and reliability (Cronbach α=.74-.85).

### Physiological Outcome Measures

The physical health outcomes survey will include measures of blood pressure (BP), resting HR, body weight (BW), height, waist circumference (WC), and hip circumference (HC). BP will be measured using an automated BP monitoring device. The participants will be given a 10-minute rest before the measurement. The BP will be measured twice, with a 1-minute interval between the readings. Additional readings will be obtained if the BP measurements differ by >5 mmHg. The mean of the 3 consecutive readings will be used as the examination value. The resting HR will be measured through a wireless HR monitor that will be worn by the participants (Polar Electro Oy) for 1 minute after their 10-minute rest. BW and height will be measured using an electronic digital scale and a stadiometer, respectively. BMI will be calculated by dividing BW (kg) by height (m^2^). The WC and HC measurements will be adopted from the study by Bacopoulou et al [69]. The WC and HC will be measured twice using an anthropometric tape while the adolescents stand erect and relaxed with their arms at their sides and feet positioned close together. The WC will be measured between the upper border of the iliac crest and the lowest border of the rib cage at the end of normal expiration. The HC will be measured at the widest part of the hip at the level of the greatest trochanter. For all the measurements, the tape will be positioned at a level that is parallel to the floor. Furthermore, the unit of measure will be in centimeters to the nearest 0.1 centimeter. The waist-to-hip ratio will be calculated as the ratio of the waist-to-hip circumference. All physical data will be recorded in the resting state at the baseline each week and at the end of training. The measurement for the physical health outcome assessment will be performed by a trained research assistant.

### Data Analysis

Interim analysis will not be performed, and data analysis will only begin after the follow-up stage. The PI and trained research assistants will have access to the final trial data set. Data will be analyzed using SPSS version 26. A missing value analysis procedure will be conducted to detect the missing values in the data file. The demographic characteristics of the participants will be investigated using the chi-square test for independence (for nominal variables) and 1-way ANOVA (for continuous variables). A Bonferroni post hoc test will subsequently be conducted for group comparisons. To examine the changes between and within groups for each outcome measure (ie, self-efficacy, mood, enjoyment, working memory, cognitive flexibility, inhibition, depression, anxiety, and stress), a 3 (before intervention vs after intervention vs follow-up) × 3 (aerobic exercise vs HIIT vs control) repeated-measure ANOVA will be conducted. A post hoc analysis will be used to confirm whether significant differences for any of the outcome variables exist among the groups. The Bonferroni method will be used to adjust the *P* values.

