### Participants

G*Power [47] was used to estimate the sample size based on analysis of variance (ANOVA) with Cohen *f* [48] medium effect size set as 0.25 and Cronbach α, as .05. A total of 45 participants are required to achieve sufficient statistical power. Assuming a 20% attrition rate [49] and clustering effect (assumed as 0.01) [50], the principal investigator (PI) will gather a total of 78 participants aged between 12 and 15 years from 3 to 4 secondary schools in Hong Kong. Each group will comprise 33% (26/78) of participants.

We will conduct the study across 3 to 4 secondary schools that will be randomly selected. Students will be invited to participate in the study given that they (1) are aged between 12 and 15 years and (2) belong to a family with a household income below half of the median household income reported in Hong Kong, which is adjusted by household size. These selection criteria are based on a study by Costigan et al [8], which examined the effect of HIIT on cognitive and mental health among adolescents. Participants (1) with hypertension or diabetes mellitus without control; (2) with a history of brain injury and other neurological diseases, epilepsy, or myocardial infarction; (3) with recent musculoskeletal disease; (4) who use medication that affects HR (eg, *β*-blockers, asthma medications, stimulants, digoxin, and antiarrhythmic agents); or (5) with cardiovascular disease will be excluded from this study. All participants in the exercise groups must complete a Chinese version of the Physical Activity Readiness Questionnaire for a safe preliminary screening before the exercise class [51].

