## Discussion

This project aims to examine whether aerobic exercise and HIIT can improve cognitive functions and well-being (eg, enjoyment) and reduce ill-being (eg, negative affect) among adolescents with low SES. Measures of subjective well-being indicators can be beneficial in examining the need for certain policies and measuring the outcomes of policy interventions. The positive findings of this study may yield a low-cost and effective intervention that enhances the overall mental health of adolescents, particularly of those living in low-income families. Despite these strengths, there are some limitations that must be considered in this study. It is anticipated that only participants with a high level of interest and motivation will enroll in exercise training. The study could be discontinued because of the current COVID-19 pandemic situation and some participants may drop out. To ensure adequate statistical power to detect statistical significance, a 20% dropout rate will be taken into account when estimating the initial sample size before the intervention. In summary, this study demonstrates the important role of regular exercise—during or after school—on the mental health of adolescents. Ultimately, we believe that such efforts will inspire policy makers to realize the benefits of physical activities at school and the importance of enabling students to integrate physical exercise into their lives.

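### The named repeated-measures ANOVA uses only participants with all three scores, so the assumed 20% attrition would discard observed posttest data and could bias the posttest contrast

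*Protocol article*

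**What the plan says.** The Data Analysis section fixes the software ("Data will be analyzed using SPSS version 26") and the model for every outcome: "a 3 (before intervention vs after intervention vs follow-up) × 3 (aerobic exercise vs HIIT vs control) repeated-measure ANOVA will be conducted". Its only statement on incomplete data is "A missing value analysis procedure will be conducted to detect the missing values in the data file". It does not say what follows once missing values are found.

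The protocol expects loss. The Participants section assumes 20% attrition when raising the required 45 participants to 78 (26 per group). The Discussion warns that "The study could be discontinued because of the current COVID-19 pandemic situation and some participants may drop out", and answers that "a 20% dropout rate will be taken into account when estimating the initial sample size before the intervention". The last assessment comes 3 months after the programme ends (Procedures), so a participant can have baseline and posttest scores but no follow-up score.

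**The concern.** A classical repeated-measures ANOVA, as run by the SPSS general linear model procedure, deletes any participant whose row lacks one of the three scores. Missing the 3-month visit therefore removes that participant's posttest score from the posttest comparison, although it was measured. Detecting missing values does not put the participant back.

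Enlarging the sample for 20% dropout protects precision but not the balance that randomisation created. The arms differ in burden: 60-minute aerobic sessions, 30-minute maximal-effort HIIT sessions, and other physical activities for controls. Outcomes such as enjoyment, mood and self-efficacy could plausibly influence who carries on. If dropout is related to outcome and the relation differs by arm, the completers in the arms are no longer comparable. The aerobic-versus-HIIT question depends on that comparability.

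**Working it through.** **Inputs from the protocol.** N = 78, 26 per arm; attrition 20%; required N = 45; Cohen f = 0.25; α = 0.05; three groups, three time points. Power and the correlation between repeated scores are not stated, so both are assumed below.

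**1. The stated 45.** For the group-by-time interaction, λ = f² × N × m / (1 − ρ), df1 = (3 − 1)(3 − 1) = 4, df2 = (N − 3)(3 − 1). With ρ = 0.5 and N = 45, λ = 0.0625 × 45 × 3 / 0.5 = 16.875, df2 = 84, and power is 0.911. So 45 is reproduced as the smallest balanced N for 90% power at ρ = 0.5. Other pairs of power and ρ also give 45.

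**2. How many enter each outcome ANOVA.** 78 × 0.20 = 15.6, so about 16 are left out. 78 × 0.80 = 62.4, so about 62 remain (26 × 0.80 = 20.8, about 21 per arm). If instead 20% were lost independently at each of the two post-baseline visits (an assumption), 78 × 0.8² = 49.9, so about 50 remain.

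**3. Power among completers.** With N = 62 and ρ = 0.5, λ = 0.0625 × 62 × 3 / 0.5 = 23.25, df2 = 118, and power is about 0.98 before any allowance for clustering.

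**4. Possible bias (illustration; all settings assumed).** Two arms, no true effect, equal correlations of 0.5, 20% loss in each arm. Loss is random in control. In the exercise arm, loss after posttest is more likely with a poor posttest score, at log-odds 1 or 1.5 per SD. The table gives the completers' between-arm difference in change from baseline, in SD, from a large-sample simulation; positive values favour exercise.

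| Dropout setting | Posttest change | Follow-up change |
|---|---|---|
| All loss after posttest, outcome-related in the exercise arm only | 0.09 to 0.11 | about 0 |
| Half the loss random and before posttest, the rest as above | 0.05 to 0.07 | about 0 |
| Same outcome-related mechanism in both arms | about 0 | about 0 |

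The first row follows from simple arithmetic. Selection raises the exercise completers' mean posttest score by about 0.17 to 0.23 SD. Their baseline rises by 0.5 times that, so the change contrast is off by 0.17 × 0.5 = 0.085 to 0.23 × 0.5 = 0.115. Follow-up rises by the same amount as baseline, so the follow-up change contrast cancels. That cancellation depends on the equal correlations assumed. Using every observed posttest score, the posttest change contrast is about 0 in all these settings.

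**5. Size against sampling error.** With 21 completers per arm and ρ = 0.5, the change score has variance 2(1 − 0.5) = 1, so SE = √(2/21) = 0.31 SD. A bias of 0.09 to 0.11 is about a third of that (0.09/0.31 = 0.29; 0.11/0.31 = 0.36). It raises a nominal two-sided 5% error rate to about 6.0% to 6.5%.

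**The case against.** The strongest objection is that this is a condensed article. It never says that incomplete cases will be excluded, and imputation before the ANOVA would be compatible with its text. That is fair as far as it goes, and imputation described elsewhere would change the result. It does not rescue the method as written, because the named procedure cannot use an incomplete row and the only step stated is detection.

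Three stronger readings are tempting, and the documents do not support them.

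- *Every analysis loses 16 participants.* The baseline chi-square tests and one-way ANOVAs do not need three visits. The 20% is a sizing assumption, not a forecast by visit.
- *The randomised comparison will be biased.* No passage says that dropout will depend on outcome or differ by arm. Pandemic-related loss need do neither. If the mechanism is the same in all arms, the bias is about 0. The only timing the protocol mentions is early withdrawal during the intervention, and loss before posttest reduces the illustrated bias.
- *The trial will be underpowered.* About 62 completers exceed the stated 45.

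It is also fair to say that a mixed model is no complete cure. It is unbiased here because dropout was made to depend on an observed score. With dropout driven by unobserved well-being it would be biased too. With baseline as a covariate, it recovers nothing from participants who have no post-baseline score.

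**Conclusion.** The concern holds in a limited form. As written, the analysis of each outcome would rest on about 62 of 78 participants if the assumed attrition occurs. Observed posttest scores would be lost for anyone who misses only the follow-up visit; that part follows directly from the method unless imputation is added. Bias in the posttest contrast is a risk rather than a certainty. It is about 0.09 to 0.11 SD under outcome-related, arm-specific dropout after posttest with correlation 0.5, about 0.05 to 0.07 SD if half the loss is random and earlier, and about 0 if the mechanism is common to all arms. Even the larger figure is about a third of a standard error. The case for change is that the loss is avoidable and a better method is available in the same software.

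**What to change.** Make the analysis of each outcome a linear mixed model (SPSS MIXED) on participants as randomised, using every available posttest and follow-up score. Fixed effects: group, categorical time, group-by-time, baseline score, and school, since recruitment is by school and the sample size allows for clustering. Use an unstructured within-person covariance. Report the group contrasts at posttest and at follow-up. Keep the complete-case repeated-measures ANOVA as a sensitivity analysis. State that the model assumes missing at random and does not recover participants with no post-baseline score.

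The cost is a change of wording and slightly more analysis work. No new software, data or participants are needed. Analysis starts only after follow-up, so the change can be made before any outcome is examined.
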